screening and delirium screening, we also reviewed the broader literature on brief
tests for general cognitive impairment (including dementia). In the context of
designing a screening tool for the acute hospital, it is important to note that
delirium generally causes cognitive impairment detectable on the kinds of tests used
for dementia screening.^36 37^ Therefore,
abnormal test results may indicate delirium and/or dementia (as well as other causes
of cognitive impairment, such as learning disability).

It is clinically essential to know if any such impairment is acute, that is,
delirium, but also important to identify underlying general (acute or chronic)
cognitive impairment. A tool designed exclusively to detect cognitive impairment will
not lead to delirium detection without another step, and a tool designed only to
detect delirium may miss general cognitive impairment. In this light, we decided that
the 4 ’A’s Test (4AT) should include cognitive screening
sensitive to general cognitive impairment, but also including items on altered level
of alertness and change in mental status, both of which are strong indicators of
delirium.

The first version of the 4AT was drafted and tested informally by colleagues, changes
were made based on feedback and updated versions were tested again. After
several iterations involving 20 doctors and nurses of varying levels of experience,
the final version was produced. An initial audit in 30 inpatients comparing clinical
use of 4AT with independent reference standard DSM-IV assessment found 100%
sensitivity (CI 69% to 100%) and 90% specificity (CI 68% to 99%). A subsequent
validation study in Italy involving 234 consecutively recruited older hospitalised
patients found that the 4AT had a sensitivity of 89.7% and a specificity
of 84.1% for delirium.^38^ The area under
the receiver operating characteristic (ROC) curves for delirium diagnosis was
0.93. Since the 4AT was launched, locally and through the www.the4AT.com website,
it has been adopted in clinical units in several centres in the UK and
internationally.

Thus, in 2014, there was encouraging evidence that the 4AT has value as a tool for
delirium detection in routine practice. This evidence came from several sources: one
published study, audits in several sites, informal feedback, adoption in clinical
practice by several clinical units globally and a recent web-based survey focused
specifically on 4AT provided evidence supporting its use. Since this study was

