### Sample size calculation

Four hundred and fifty patients will be randomised to assessment by 4AT and 450 to
CAM. We will recruit sufficient patients to account for attrition, though we do not
expect significant attrition because the recruitment, consenting and assessment
process takes place over a small number of hours in a single episode. Of the 450
patients within each assessment arm, 15% (67) would be expected to have delirium. The
specificity of the triage tool would be estimated based on the 85% (383) without
delirium, while the sensitivity would be estimated from the 67 with delirium. Based
on the analysis using the normal approximation to the binomial distribution,
the two-sided 95% CI widths for the specificity and sensitivity would be as shown in
table 1 for a range of levels of diagnostic
test performance.

**Table 1 T1:** Precision of specificity, sensitivity estimation

Parameter	True level of parameter	95% CI width
Specificity	0.5	±0.050
Specificity	0.7	±0.046
Specificity	0.9	±0.030
Sensitivity	0.5	±0.120
Sensitivity	0.7	±0.110
Sensitivity	0.9	±0.072

It will therefore be possible to estimate the specificity precisely and the
sensitivity with moderate precision. The precision in estimating negative predictive
value would be expected to be similar to that for specificity; for positive
predictive value, it would be expected to be similar to that for sensitivity. For the
secondary objective of comparing 4AT and CAM, based on analysis by continuity
corrected χ^2^ test, we have 83% power to detect a difference in
specificity of 0.1, assuming a null hypothesis of specificity=0.70 for both
tests and a two-sided 5% significance level. The corresponding difference detectable
for sensitivity (null hypothesis sensitivity=0.7) would be 0.224 with 80% power.

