#### Secondary objectives

4AT versus CAM: differences in each of sensitivity, specificity, positive
and negative predictive values between 4AT and CAM will be tested by
Fisher’s exact test and quantified by the difference in the two
proportions (4AT-CAM) and its 95% CI. To aid comparison of 4AT and CAM, the
overall performance of each will also be summarised using Youden’s
Index (sensitivity minus false positive rate) and the OR of sensitivity to
specificity.Performance of the 4AT cognitive screening items: Is the 4AT an adequately
sensitive tool for detecting general cognitive impairment as judged against
a documented history of dementia and/or the IQCODE? This objective will be
addressed using the same methods as for the primary objective.4AT versus clinical outcomes: as assessment of criterion validity, we will
assess the performance of the 4AT in predicting length of stay,
institutionalisation and mortality up to 12 weeks. Descriptive
statistics of clinical outcomes will be presented for the groups with and
without 4AT scores above the cut point of 3. The relationship between 4AT
and each of mortality and institutionalisation will be analysed via logistic
regression modelling; Kaplan-Meier curves and the Cox proportional hazards
model will be used to assess 4AT as a predictor of hospital length of stay.
The logistic regression and Cox models will adjust for age, gender and
presence of dementia.Individual items: we will conduct analyses examining performance of
individual items of the 4AT, for example, is altered level of
alertness alone a good predictor of delirium diagnosis? (methods as per
primary objective);Delirium severity: we will assess the 4AT total score as a measure of
delirium severity by calculating the Spearman correlation between 4AT and
DRS-R98 scores and its 95% CI.

Full details of the proposed statistical analyses for the primary objective and
secondary objectives (a)–(e) will be documented in a SAP which will include
details of methods for calculating derived variables, any sensitivity and subgroup
analyses and approaches to testing the assumptions in the statistical analyses.
The SAP will outline the plan for validation of the statistical analysis.

Individuals with missing data for the reference diagnostic test will be removed
from formal statistical analysis. Where any items of the CAM or 4AT were not able
to be assessed, an overall delirium diagnosis will still be derived where possible

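### The odds ratio chosen to summarise overall performance of 4AT and CAM measures, as worded, the balance between sensitivity and specificity, not accuracy

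*Protocol article*

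**What the plan says.** The 4AT versus CAM item under Secondary objectives in the protocol article has two layers. The inferential layer compares sensitivity, specificity and both predictive values between the tests by Fisher's exact test, with a difference in proportions and 95% CI for each. A descriptive layer follows: the "overall performance of each will also be summarised using" two indices, namely Youden's "Index (sensitivity minus false positive rate) and the OR of sensitivity to specificity". The first is defined in brackets as sensitivity less the false positive rate. The second is given only by the closing words of that quote.

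The article gives no formula for this odds ratio and does not mention a diagnostic odds ratio. Details of derived variables are left to a SAP that is not at hand.

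**The concern.** An odds ratio of one proportion to another is the odds of the first divided by the odds of the second. Applied to sensitivity and specificity, this puts the odds of a correct result in patients with delirium over the odds of a correct result in patients without it. Both are desirable, and dividing one by the other cancels what they have in common. What remains shows which of the two is larger, not how well the test discriminates.

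The usual single-number odds ratio for a diagnostic test sets sensitivity against the false positive rate. That is the same pairing the sentence uses correctly for Youden's Index a few words earlier.

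At stake is one of the two single-number summaries offered for the first-listed secondary objective. A literal value such as 1.65 looks plausible, so it could be programmed, reported and read as accuracy without anyone noticing.

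**Working it through.** **Inputs**
- The measure and its purpose: Secondary objectives, as quoted above.
- Illustrative levels 0.5, 0.7 and 0.9: Table 1 in Sample size calculation, given there "for a range of levels of diagnostic test performance".
- Planning values for the 4AT versus CAM comparison: "assuming a null hypothesis of specificity=0.70 for both" tests, and "null hypothesis sensitivity=0.7".
- Earlier 4AT results from Rationale for the study: "the 4AT had a sensitivity of 89.7"%, with specificity 84.1%.
- The pair 0.9/0.1 is my own example of an uninformative test (Se = 1 - Sp).

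The article states no value for this measure, so there is no figure to reproduce.

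**Formulas**, with odds(p) = p/(1-p)
- Odds ratio as worded: odds(Se)/odds(Sp)
- Diagnostic odds ratio (DOR), sensitivity against the false positive rate: odds(Se)/odds(1-Sp) = odds(Se) x odds(Sp) = (Se x Sp)/[(1-Se)(1-Sp)]
- Youden's Index: Se - (1-Sp) = Se + Sp - 1

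**Worked example at the earlier 4AT results.** odds(0.897) = 0.897/0.103 = 8.709 and odds(0.841) = 0.841/0.159 = 5.289. As worded: 8.709/5.289 = 1.65. DOR: 8.709 x 5.289 = 46.1. Youden: 0.897 + 0.841 - 1 = 0.738.

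| Se | Sp | As worded | DOR | Youden |
|---|---|---|---|---|
| 0.5 | 0.5 | 1.0 | 1.0 | 0.0 |
| 0.7 | 0.7 | 1.0 | 5.44 | 0.4 |
| 0.9 | 0.9 | 1.0 | 81 | 0.8 |
| 0.9 | 0.7 | 3.86 | 21 | 0.6 |
| 0.7 | 0.9 | 0.26 | 21 | 0.6 |
| 0.9 | 0.5 | 9.0 | 9.0 | 0.4 |
| 0.9 | 0.1 | 81 | 1.0 | 0.0 |
| 0.897 | 0.841 | 1.65 | 46.1 | 0.738 |

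**What the table shows**
1. Whenever Se = Sp the worded measure is 1, whether the test is uninformative (0.5/0.5) or good (0.9/0.9).
2. With sensitivity held at 0.9, lowering specificity from 0.9 to 0.7 to 0.5 moves the worded measure up (1.0, 3.86, 9.0) while Youden falls (0.8, 0.6, 0.4). The two summaries in the same sentence then rank the tests in opposite order.
3. Two tests with equal Youden (0.6) and equal DOR (21) receive 3.86 and 0.26.
4. The uninformative test at 0.9/0.1 scores 81. The earlier 4AT results score 1.65.

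**At the article's own planning contrast.** Take both tests at sensitivity 0.7, one with specificity 0.7 and the other 0.1 higher at 0.8 (taking the planned difference upwards is my assumption). As worded: (0.7/0.3)/(0.7/0.3) = 1.0, against (0.7/0.3)/(0.8/0.2) = 2.333/4 = 0.58. DOR: 2.333 x 2.333 = 5.44, against 2.333 x 4 = 9.33. Youden: 0.4 against 0.5. The test that is better on both DOR and Youden gets the lower worded value.

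Reading the measure as distance from 1 does not rescue it, because 0.5/0.5 and 0.9/0.9 are both exactly 1.

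**The case against.** The strongest reply is about reach. The sentence is explicitly an addition. Inference on 4AT versus CAM rests on the Fisher tests and on the differences with confidence intervals, none of which use this odds ratio. No test, decision rule or sample size depends on it, and the primary analysis does not use it. Youden's Index stands beside it, so a reader who saw an odds ratio near 1 next to a Youden of 0.74 would have the means to notice. It can also be recalculated at any time from the same two-by-two tables. All of this stands, and it limits the severity.

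A second reply is that the phrase may be loose shorthand for the diagnostic odds ratio, since the stated purpose points that way, and that the SAP may define it so. That is possible and cannot be checked here. It does not remove the point: this is not detail left for later but a named measure given a purpose it cannot serve. A SAP that followed the wording would carry the error forward, and one that used the DOR would differ from the published text.

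Three stronger readings are tempting and should not be drawn:
- A reader might infer that the 4AT versus CAM comparison as a whole is unsound. It is not, because its inferential part is untouched.
- A reader might infer that the trial has in fact inverted the second odds, or that the SAP is wrong. The article shows only a phrase without a formula.
- A reader might infer that every useless test scores 1. The value 1 arises only when Se = Sp. Uninformative tests in general give [Se/(1-Se)]^2, for example 81 at 0.9/0.1.

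**Conclusion.** The point holds on the text. The odds ratio named in the protocol article, taken literally, shows the balance between sensitivity and specificity and cannot summarise overall performance. At the earlier 4AT results the literal value is 1.65 where the DOR is 46.1.

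The conclusion that the summary would mislead rests on one assumption: that the phrase is computed as worded. The effect is confined to a supplementary descriptive summary within a secondary objective, so I grade it moderate to minor.

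**What to change.** In the 4AT versus CAM item, replace the phrase with: the diagnostic odds ratio, that is, the odds ratio of sensitivity to the false positive rate, (Se x Sp)/[(1-Se)(1-Sp)], with 95% CI, for each test. Check that the SAP gives the same formula, and state there what is done if a cell of the two-by-two table is zero.

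Dropping the odds ratio and keeping Youden's Index is an acceptable alternative. If the literal ratio is wanted for its own sake, describe it as a measure of balance between sensitivity and specificity and not as overall performance.

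The cost is one line of text in the protocol, and one in the SAP if it repeats the wording. No data collection, sample size or other analysis changes.

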### Randomisation procedure

The allocation sequence will be created using computer-generated random numbers.
Participants will be randomised in a 1:1 ratio to be assessed using the 4AT or CAM
experimental assessment. The order in which they receive the reference standard and
experimental assessment will also be randomised in a 1:1 ratio. Randomisation will be
stratified by study site with block allocation. The randomised allocations will be
concealed until they are assigned, as the randomisation system will be
web based and requires a personal login and password. Once randomisation has
been performed, neither the researchers nor the participant will be blinded to the
allocation as both will be aware of the assessments conducted and the order in which
they are performed.

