### Outcome measurements (what, when, how)

Note that the outcome measurements for the primary study (the reference standard) are
performed at almost the same time as the 4AT and CAM. The only subsequent data
collection is capturing clinical outcomes at 12 weeks. This will be achieved
through searching electronic patient records, telephone calls with participants or
face-to-face interviews if still in hospital. The information gleaned at the
12-week point will at times be generalised due to participant recall or availability
of full electronic records.

(1) Primary outcome measure:

Diagnostic accuracy of the 4AT versus the reference standard delirium diagnosisSecondary outcome measures:4AT versus CAM in relation to reference standard delirium diagnosis.Performance of 4AT cognitive test items (AMT4 and Months Backwards) in
detecting longer term cognitive impairment as detected by the
IQCODE.4AT total scores as a predictor of the following clinical outcomes as
determined at 12 weeks post-test: length of stay, falls,
institutionalisation (as assessed by proportion of patients newly admitted
to care homes or awaiting care homes at that time) and mortality.Performance of individual items of the 4AT in relation to reference standard
delirium diagnosis.We will assess the 4AT total score as a measure of delirium severity.The primary output from the health economic analysis will be a comparison of
the service delivery costs associated with the diagnostic accuracy of
alternative (4AT vs CAM vs reference standard) triage tools for
delirium.

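### Length of stay by Kaplan-Meier makes no provision for in-hospital death, and new institutionalisation is a proportion of patients without an at-risk denominator; both should be fixed before the 4AT is judged as a predictor

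*Protocol article*

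**What the plan says.** The Data analysis plan (Secondary objectives, 4AT versus clinical outcomes) sets out, as criterion validity, to "assess the performance of the 4AT in predicting length of stay", institutionalisation and mortality up to 12 weeks. The relationship between the 4AT "and each of mortality and institutionalisation will be analysed via logistic" methods. For length of stay the text reads "regression modelling; Kaplan-Meier curves and the Cox proportional hazards" and continues "model will be used to assess 4AT as a predictor of hospital length of stay". On covariates it says "The logistic regression and Cox models will adjust for age, gender and" dementia.

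The section Outcome measurements (what, when, how) defines the care-home outcome as "institutionalisation (as assessed by proportion of patients newly admitted" to a care home, or waiting for one, at 12 weeks.

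Neither section says whether death in hospital is an event, a censoring or something else for length of stay. Neither says who forms the denominator for institutionalisation. Care-home residence is not among the exclusion criteria, so existing residents can be enrolled. The article leaves derived variables, sensitivity analyses and checks of assumptions to a SAP that is not shown.

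**The concern.** The cohort is aged 70 or over and acutely ill, and the same objective asks whether the 4AT predicts death over the same 12 weeks. If it does, deaths are unevenly spread across the two groups whose stay and care-home admission are compared.

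A patient who dies in hospital can never be discharged alive. Kaplan-Meier has no place for such an event: the two usual ways of coding it either overstate discharge or turn an early death into a short stay.

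A patient already in a care home cannot be newly admitted, and one who dies before any such move cannot be in or waiting for a care home at 12 weeks. If both stay in the denominator they count as good outcomes. If both are commoner among 4AT-positive patients, the association with the 4AT is diluted. At stake is how well the 4AT appears to predict two of the named clinical outcomes.

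**Working it through.** The plan gives no figure for this analysis, so there is none to reproduce. It also gives no mortality, discharge rate or care-home share by 4AT result. Every rate below is an assumption, chosen to show direction and range. The horizon is 12 weeks, or 84 days.

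**1. Length of stay, deaths censored.** Take constant daily hazards, h_d for live discharge and h_m for in-hospital death.
- True proportion discharged alive by day t: h_d/(h_d+h_m) × (1 − exp(−(h_d+h_m)t))
- Kaplan-Meier with deaths censored: 1 − exp(−h_d·t)

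With a total exit rate of 1/14 per day in 4AT-positive patients:

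| Share dying in hospital | Day | Kaplan-Meier | True |
|---|---|---|---|
| 15% | 28 | 1 − exp(−1.7) = 0.817 | 0.85 × (1 − exp(−2)) = 0.735 |
| 15% | 84 | 1 − exp(−5.1) = 0.994 | 0.85 × (1 − exp(−6)) = 0.848 |
| 20% | 28 | 1 − exp(−1.6) = 0.798 | 0.80 × (1 − exp(−2)) = 0.692 |
| 20% | 84 | 1 − exp(−4.8) = 0.992 | 0.80 × (1 − exp(−6)) = 0.798 |

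A second set of assumptions agrees in direction. With h_d = 0.05 in 4AT-positive patients and h_m = 0.003, 0.006 or 0.012, the true day-84 figure is 0.932, 0.885 or 0.802, while Kaplan-Meier gives 0.985 each time. The overstatement is 5 to 18 points. In 4AT-negative patients (h_d = 0.10, h_m = 0.003) it is 3 points: 1.000 against 0.971.

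**2. Length of stay, death counted as the end of stay.** The hazard ratio (4AT-positive to negative) becomes (h_d1+h_m1)/(h_d0+h_m0) in place of h_d1/h_d0. With h_d0 = 0.10 and h_m0 = 0.003:
- h_d1 = 0.05, discharge ratio 0.50: with h_m1 = 0.003, 0.006 or 0.015 the ratio is 0.053/0.103 = 0.51, 0.056/0.103 = 0.54 or 0.065/0.103 = 0.63.
- h_d1 = 0.08, h_m1 = 0.02: the discharge ratio is 0.80, and the ratio obtained is 0.100/0.103 = 0.97.

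**3. Institutionalisation.** Let r be the risk of new admission among survivors who came from the community, d the proportion who die and c the proportion already in a care home. With everyone in the denominator, the observed proportion is (1−c)(1−d)r.
- Assume r = 20% against 8%: OR = (0.20/0.80)/(0.08/0.92) = 2.875.
- c = 10% against 3%, d = 15% against 5%: 0.90×0.85×0.20 = 0.1530 and 0.97×0.95×0.08 = 0.0737, so OR = 2.27.
- c = 20% against 5%, d = 20% against 7%: 0.80×0.80×0.20 = 0.1280 and 0.95×0.93×0.08 = 0.0707, so OR = 1.93.

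With r = 20% against 5% (OR 4.75), the OR becomes 3.82 if deaths of 20% against 5% count as non-events, 4.11 if prior residents of 15% against 5% stay in the denominator, and 3.33 with both. These are crude odds ratios. The planned adjustment for age, gender and dementia may absorb part of the imbalance in prior residence.

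**The case against.** The strongest reply is that the article does not say what it does with deaths, and that coding, analysis sets and derived variables belong in the SAP. This stands as far as certainty goes: the bias cannot be asserted as a fact of the planned analysis. It does not remove the point, because the article already fixes the estimator. Kaplan-Meier would give the cumulative incidence of live discharge only if those who died were held at risk to day 84, and nothing suggests that.

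Several stronger readings are tempting and should be resisted:
- A reader might infer that the plan forgets that some patients already live in care homes. It does not: the outcome is new admission, so prior residence is recognised in the event. Only the denominator is open.
- A reader might infer that the Cox model is wrong. With deaths censored it is a valid cause-specific model for live discharge, limited in interpretation but not invalid. In the example with a discharge ratio of 0.50, it would still estimate 0.50.
- A reader might infer that site must be in the models because randomisation was "stratified by study site with block allocation". That argument concerns the randomised contrast ("Participants will be randomised in a 1:1 ratio to be assessed using the 4AT or CAM"). Here a non-randomised score is related to outcome.

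Two further objections have some force. With death as the end of stay, Kaplan-Meier correctly describes time in a bed; but as evidence that a test identifies patients who do worse, a stay shortened by death misleads. Likewise, the proportion of all patients newly in a care home is a legitimate quantity, but it is not the risk among those who could move to one, and the article does not say which is wanted.

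**Conclusion.** The point holds in a limited form. Kaplan-Meier is named for length of stay with no provision for in-hospital death as a competing event, and both usual codings distort the comparison by 4AT result. The care-home outcome, read literally, keeps existing residents and those who died as non-events, which probably dilutes the association with the 4AT.

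Under the assumed rates, live discharge at day 84 in 4AT-positive patients is overstated by about 5 to 19 points, and an institutionalisation odds ratio of 2.875 falls to 2.27 or 1.93. The true size cannot be fixed from the document. It depends on the unstated coding of deaths, on mortality and prior residence by 4AT result, and on what the adjusted models absorb. The direction for institutionalisation rests on death and prior residence being commoner in 4AT-positive patients.

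One secondary objective is affected. The primary accuracy estimates and the comparison of 4AT with CAM are not. The change is worth making because it is nearly free.

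**What to change.** 1. Length of stay: present cumulative incidence curves of discharge alive, with in-hospital death as a competing event, in place of Kaplan-Meier. Keep the Cox model, stated explicitly as a cause-specific model for live discharge, and report the cause-specific model for in-hospital death beside it.
2. Institutionalisation: restrict the analysis to patients not in a care home at baseline. Report deaths explicitly, either through a three-level multinomial outcome (home, care home, dead) or through a sensitivity analysis of new care home or death.
3. Optionally, add site as a covariate, on the ground that discharge and care-home practice may differ between the three sites.

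The cost is SAP wording, standard software and a little more analysis work. Length of stay and mortality are already to be collected at 12 weeks, and baseline residence is needed anyway to identify new admissions. The downside is a slightly smaller at-risk set for institutionalisation and, if site is added, two extra parameters per model.

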## Methods and analysis

### Study overview

Nine hundred patients aged 70 or over in EDs or acute general medical wards
will be recruited in three sites (Edinburgh, Bradford and Sheffield). Study
recruitment commenced on 19 October 2015. Recruitment was planned to be
completed in December 2016, with final follow-up data collection and locking of the
database in March 2017. The assessments are: (a) a reference standard delirium
assessment lasting up to 20 min and (b) either the 4AT or the CAM lasting up
to 10 min. The reference standard and 4AT or CAM assessments will take place
within a maximum of 2 hours of each other, with a target interval of
15 min. The results of the reference standard assessment were recorded in the
case notes and communicated to the clinical team after the index assessments had been
completed and recorded. The team will invite an appropriate informant to complete a
questionnaire on participant’s preadmission cognitive function. This will be
completed within 4 weeks of the patient being recruited to the study assuming an
appropriate individual is available.

At 12 weeks, the team will also administer a 10 min resource-use questionnaire
(face to face in hospitalised patients or by telephone when possible) and will access
each recruited patient’s medical records at 12 weeks to ascertain a set of key
clinical outcomes, including length of stay, institutionalisation and mortality, as
well as to derive further information on resource utilisation. The study
flow chart is shown in figure 1. The study has been registered: international standard randomised
controlled trial number (ISRCTN) 53388093. UK Clinical Research Network ID:
19 502.

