### Inclusion criteria

Aged 70 or over.Acutely admitted to the ED (within 12 hours of attending) or acute
general medical and geriatrics units (within 96 hours of admission to
the ward). For ED patients, we will only recruit from those patients who were
brought in by ambulance as an emergency or through their general
practitioner.

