### Identification of participants

The participant screening strategy in the initial protocol stated that patients will
be recruited between 08.00 and 22.00. A list of potentially eligible patients will be
generated in batches at the start of each recruitment period and initial eligibility
screening will be carried out by clinical staff (including clinical research nurses
embedded in the clinical team). Then, in alphabetical order, in each batch,
consent/agreement from patient (or proxy/consultee) will be sought by a study
researcher. Numbers of those (a) initially potentially eligible, (b) screened as
non-eligible by clinical staff and (c) declining to take part will be recorded.

This recruitment strategy was modified in the last 5 months of recruitment because
preliminary analyses suggested that patients at lower risk of delirium (ie, those not
requiring capacity assessment) were more likely to be recruited than those with
impaired capacity. Thus, to allow for some oversampling of patients at higher risk of
delirium, a pragmatic approach was adopted. From the batches of patients identified
as in the original strategy, patients considered at higher risk of delirium on
clinical grounds (eg, older age, likely to be admitted, higher degree of ongoing
acute and chronic illnesses) were approached first, rather than by alphabetical
order.

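### The length-of-stay Cox model pools ED and ward recruits with no term for recruitment setting, so the 4AT hazard ratio may partly reflect where patients were recruited

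*Protocol article*

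**What the plan says.** The study recruits one population through two routes: "Nine hundred patients aged 70 or over in EDs or acute general medical wards" (Study overview). The Inclusion criteria set different windows for each. The ED route reads "Acutely admitted to the ED (within 12 hours of attending) or acute", and the ward route reads "general medical and geriatrics units (within 96 hours of admission to" the ward. A further restriction begins "For ED patients, we will only recruit from those patients who were" and limits ED recruits to arrivals by emergency ambulance or through a general practitioner. Nothing requires an ED recruit to be admitted afterwards.

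Under Secondary objectives in the Data analysis plan, the Cox "model will be used to assess 4AT as a predictor of hospital length of stay", and mortality and institutionalisation each get a logistic model. The covariates are then named: "The logistic regression and Cox models will adjust for age, gender and" the presence of dementia. No setting term, stratum or separate analysis is stated. The SAP is left to supply derived variables, sensitivity and subgroup analyses, assumption checks and validation.

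Identification of participants says that in the last five months patients at higher risk of delirium were approached first, on "clinical grounds (eg, older age, likely to be admitted, higher degree of ongoing" illness. Randomisation is "stratified by study site with block allocation"; ED or ward is not a stratum.

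**The concern.** A ward recruit is in hospital by definition. An ED recruit may go home the same day. Setting at recruitment is therefore a plausible determinant of length of stay. It is also plausibly related to the 4AT result, because the protocol itself treats likely admission as a marker of delirium risk and as something that varies between candidates. A variable related to both the predictor and the outcome, and absent from the model, can create or distort an association.

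Randomisation gives no protection. It allocates 4AT or CAM and the order of testing. The 4AT score is observed, not allocated.

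The analysis is presented as evidence of criterion validity for the 4AT. If positive scores cluster in one setting, a hazard ratio away from 1 could arise with no relation between score and stay within either setting, and it would be read as validity. Because the covariate set is already chosen in the protocol, this is a comment on a stated model rather than on a detail left to the SAP.

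**Working it through.** The protocol states no effect size, power or result for this model, so there is no figure to reproduce. The check asks how large a spurious hazard ratio for discharge could be when the 4AT has no effect within either setting. A hazard ratio below 1 means a longer stay among 4AT-positive patients.

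**Inputs from the protocol.** n=450 with a 4AT score (Sample size calculation). Sensitivity 0.897 and specificity 0.841, from the earlier validation study in 234 patients (Rationale). Follow-up of 12 weeks = 84 days.

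**Inputs that are assumptions.** ED share of recruits 30–50%; delirium 8–10% in the ED and 15–25% on wards; median stay 1–3 days for ED recruits and 7–10 days for ward recruits; log-normal stay with SD of log stay 0.9.

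**Step 1: 4AT positivity by setting.** Positivity = Se × prevalence + (1 − Sp) × (1 − prevalence).

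- Mild corner: ED 0.897×0.10 + 0.159×0.90 = 0.233; ward 0.897×0.15 + 0.159×0.85 = 0.270.
- Extreme corner: ED 0.897×0.08 + 0.159×0.92 = 0.218; ward 0.897×0.25 + 0.159×0.75 = 0.344.

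**Step 2: imbalance in setting.**

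- Mild corner, 30% ED: the ED share among 4AT-positives is 0.3×0.233/(0.3×0.233 + 0.7×0.270) = 27%. Among 4AT-negatives it is 0.3×0.767/(0.3×0.767 + 0.7×0.730) = 31%.
- Extreme corner, 50% ED: 0.218/(0.218 + 0.344) = 39% against 0.782/(0.782 + 0.656) = 54%.

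**Step 3: spurious hazard ratio, Cox model with the 4AT result only.** Simulated in runs of 20,000 patients:

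- 30% ED, delirium 10% v 15%, stay 3 v 7 days: 0.972
- 50% ED, otherwise the same: 0.965
- 50% ED, delirium 8% v 25%, stay 1 v 10 days: about 0.83

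In intermediate scenarios within these ranges, stratifying by setting returned 0.98 to 1.01.

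**Step 4: scale.** The standard error of the log hazard ratio is about 1/√(D·p(1−p)). With nearly all 450 discharged by 84 days (assumed) and p≈0.27, this is 1/√(450×0.27×0.73) = 0.106, say 0.11. Then |ln 0.972|/0.11 = 0.26, |ln 0.965|/0.11 = 0.32 and |ln 0.83|/0.11 = 1.7.

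**Step 5: separate simulation with age, gender and dementia in the model.** n=450, 300 replicates, exponential stay, true 4AT effect null. The 4AT-positive proportions and the ED:ward ratio of discharge hazards are assumed.

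| ED share | 4AT+ ED / ward | Hazard ratio ED:ward | 4AT HR, planned covariates (rejection rate) | 4AT HR with setting added (rejection rate) |
|---|---|---|---|---|
| 50% | 10% / 20% | 1.5 | 0.94 (0.11) | 1.01 (0.08) |
| 50% | 10% / 20% | 2 | 0.89 (0.13) | 1.01 (0.05) |
| 50% | 10% / 20% | 3 | 0.84 (0.26) | 1.00 (0.04) |
| 30% | 10% / 20% | 2 | 0.92 (0.08) | 1.00 (0.05) |
| 50% | 13% / 17% | 2 | 0.95 (0.04) | 1.01 (0.04) |
| 50% | 15% / 15% | 2 | 1.00 (0.04) | 0.99 (0.04) |
| 50% | 20% / 10% | 2 | 1.14 (0.19) | 1.01 (0.07) |

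The nominal rejection rate is 0.05, with Monte Carlo error √(0.05×0.95/300) = 0.013. Age, gender and dementia were drawn independently of setting here, so they could not absorb any of its effect. In the real data they might absorb some.

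**The case against.** The strongest reply has four parts.

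First, nothing in the protocol shows that the bias exists. It gives no delirium rate, 4AT positivity, length of stay or admission rate by setting. ED recruits are restricted to ambulance and general practitioner arrivals, and the late change in recruitment favoured those likely to be admitted. Both may narrow the gap between settings. This stands. A reader might infer that the 4AT will look predictive of longer stay because of setting, but the documents do not support a direction: with equal positivity there is no bias, and with higher positivity in the ED the sign reverses.

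Second, older age is listed beside likely admission as a risk marker, so the planned age term may already remove part of any setting effect. This also stands, and it means the range without covariates is not an estimate for the planned model.

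Third, the aim is prediction, and delirium may itself influence who reaches a ward, so stratifying could remove genuine signal. This is a real trade-off, but it does not defeat the point. The plan already adjusts for patient characteristics, setting is known for every patient before the 4AT is done, and both results can be reported.

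Fourth, subgroup analyses and assumption checks are left to the SAP. That is so. A reader might add that one baseline hazard cannot fit both settings because ED patients have an early discharge peak. No section says they do, and checking proportional hazards belongs to the SAP. The covariate list, however, is fixed in the protocol.

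**Conclusion.** The point holds for the length-of-stay model. As specified, its 4AT hazard ratio cannot be separated from recruitment setting if 4AT positivity differs between ED and ward. The size and direction cannot be derived from the protocol. With more delirium assumed on wards, no true effect within setting and no covariates, the spurious hazard ratio is about 0.83 to 0.97, or roughly 0.3 to 1.7 standard errors. The mild end is negligible; the extreme end is enough to mislead.

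Two further readings are not supported. One might infer the same bias for mortality and institutionalisation. The covariate list is shared, but no bias there has been quantified. One might also read this as a threat to the study's main conclusion. It is not: sensitivity, specificity and predictive values do not use these models. The change is worth making because it is cheap and affects a stated secondary objective.

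**What to change.** In the SAP, before database lock:

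- Stratify the length-of-stay Cox model by setting at recruitment (ED or ward). Do not use later admission from the ED for this, since it may be a consequence of delirium.
- Show the Kaplan-Meier curves by 4AT result separately for ED and ward recruits.
- Report the planned pooled model, adjusted for age, gender and dementia, alongside, so that a reader can see how far the estimate moves.
- Optionally add setting to the two logistic models. This is a reasonable low-cost extension rather than a correction of a demonstrated bias.

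The cost is one stratum, or one degree of freedom in each logistic model, and no new data. The downside is that some predictive signal may be removed if delirium influences admission to the ward, which is the reason for keeping the pooled result in the report.
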